### Eligibility criteria

To be included in the study a participant must meet the following criteria: 1) parent that is ≥18 years old with a child 3–5 years old enrolled in participating schools (Poplar or Wolf Point); 2) willingness to participate in all aspects of the study including random assignment; 3) parent has experienced at least one ACE, and recent or historical trauma; and 4) the child is an enrolled member or the descendant of an enrolled member of the Fort Peck Tribes. For the purposes of this study, parents are being defined as the primary caregiver of the child. Participants will be excluded if they indicate they are planning to move or know they cannot otherwise take part in the full intervention during baseline enrollment.

### Recruitment and consent/assent

Participants will be recruited through referrals from Head Start staff and through flyers and study team attendance at Head Start related events. Potential participants who express interest will be provided with a brief overview of the study and complete a phone screen to determine eligibility. Only one child per family is eligible – if more than one child in a family meets eligibility criteria, we will randomly select which child will be included in the study. If participants meet eligibility criteria, study staff will schedule a time to complete consent and baseline assessment procedures. The parent will complete the consent form for their own participation. The parent or legal guardian of the child will also provide assent for the child to participate.

### Intervention

The Little Holy One intervention combines elements adapted from *CETA* (four lessons) and *Family Spirit* (four lessons) with four cultural lessons addressing tribal-specific risk (historical trauma) and protective factors (cultural identity, communal mastery) (Table 1).

**Table 1 Tab1:** Little Holy One lessons and origin

Component	Origin	Participant(s)
Psychoeducation	*CETA*	Parent
Substance Use Prevention	*CETA*	Parent
Coping with Traumatic Stress Symptoms	*CETA*	Parent
Cognitive Coping Skills	*CETA*	Parent
Knowing Your Child	*Family Spirit*	Parent
Monitoring Your Child	*Family Spirit*	Parent
Daily Routines	*Family Spirit*	Parent
Skills for Healthy Living	*Family Spirit*	Parent
Promoting Tribal Identity	Cultural	Parent + Child
Enhancing Communal Mastery	Cultural	Parent + Child
Promoting Smudging	Cultural	Parent + Child
Healing Historical & Contemporary Trauma	Cultural	Parent

*CETA* was selected as the basis for Little Holy One for its proven ability to address stress-related problems in trauma-affected, low-resource communities [41–44]. *CETA* is originally a mental health treatment program, but we selected and adapted four *CETA* lessons and designed them to focus on prevention of mental health disorders rather than treatment. The lessons include a focus on 1) psychoeducation (Understanding Our Emotions), 2) cognitive coping skills (Thinking Positively), 3) substance use prevention (Alcohol and Drug Use), and 4) coping with traumatic stress symptoms (The Power of Our Memories) [45].

*Family Spirit* is an evidence-based intervention proven to promote positive parenting and childrens’ early social, emotional, and behavioral well-being among tribal communities [34, 46]. Original lessons were taught to parents with children ages 1–3 years but were adapted for parents of children ages 3–5 years for Little Holy One. Lesson themes include: 1) understanding children’s emotional, social, and physical development; 2) “mindful parenting”—focused on nurturing monitoring and supervision; 3) avoiding power struggles that lead to childrens’ behavioral problems by establishing healthy, consistent routines; and 4) “skills for healthy living” that promotes healthy family relationships and planning for childrens’ futures.

Four cultural lessons, developed in partnership with the Tribal Advisory Board and key community leaders, are designed to 1) promote tribal identity, 2) promote communal mastery (strengthen family and community), 3) heal historical and contemporary trauma, and 4) promote smudging as a family-based spiritual practice. Parents are receiving all 12 lessons, while children participate with their parents in three of four cultural lessons on tribal identity, communal mastery, and smudging. Children are being excluded from the fourth cultural lesson given the sensitive subject matter, and it will allow parents the space to explore historical and contemporary trauma without having to tend to their child’s needs. Each of the 12 intervention lessons are designed to be approximately one to one and a half hours in length.

### Control condition

The active control condition has interventionists that teach nutrition education topics (Table 2**)** in six group sessions of up to 7–8 parent-child dyads per group. Parents learn about healthy food options, where to access healthy foods, are given healthy recipes, and sample easy-to-make healthy foods with their children. The nutrition lessons are approximately 1 hour in length. Control content was selected by the Tribal Advisory Board based on its potential benefit and interest to participating families, with minimal risk for contaminating intervention outcomes.

**Table 2 Tab2:** Lesson schedule for all study participants

Week	Little Holy One Lessons (Intervention)	Nutrition Lessons (Control)
1	**Ą́**ba Wasté / Aŋpétu Wašté (Promoting Tribal Identity)	Racing Towards Healthy Eating
2	Understanding our Emotions	–
3	Azí’įc’iya / Azídya (Promoting Smudging)	Fun with Food Groups!
4	Thinking Positively	–
5	Encouraging Early Learning	Portion Sizes
6	Daily Routines for Caregivers and their Children	–
7	Alcohol and Drug Use	Making Your Plate
8	Monitoring your Child’s Routine	–
9	Strengthening Family and Community (Enhancing Communal Mastery)	Rethink Your Drink!
10	The Power of Our Memories	–
11	Healing Historical Trauma	Savor It: Smell, See, Taste!
12	Skills for Effective Caregiving	–

### Lesson frequency and duration

Participants in the intervention group will be taught the 12 lessons over a 16-week period in individual sessions with their community health worker—a delivery strategy selected to enhance participant engagement, local acceptability, and sustainability [47, 48]. Lessons will be delivered at a location that works best for the participant, including Head Start locations, community centers, or study office space at a convenient time (i.e., after drop-off or pick-up). Participants in the control group will participate in group or individual lessons on nutrition at a convenient time and place for participants. Both the intervention and control lessons will begin 2 weeks after study enrollment, and baseline assessments and randomizations have been completed. Participants in both conditions will be assessed by blinded evaluators using mobile data collection at baseline, 12 weeks (when intervention ends), and 6-, 12-, 18-, and 24-months follow-up. Figure 2 outlines the overall flow of the study below.

**Fig. 2 Fig2:**
[figure not shown]
Overall study flow and SCED

### Randomization process and study flow

Participants are being recruited from Poplar and Wolf Point Head Starts in four cohorts over 2 years. Two cohorts of 15 dyads will be randomized each semester to the intervention or control conditions, for a total of 30 per intervention and 30 per control each year for 2 years. Within the Little Holy One intervention, participants will be further randomized at two time points: 1) after the second lesson participants will be randomized to immediately receive a smudging lesson in session 3 or wait until session 5 to receive the smudging lesson; and 2) after the sixth session, participants will either immediately receive the communal mastery lesson in session 7 or wait until session 9 to receive the communal mastery session (Fig. 2). First-order randomization to either Little Holy One or the active control, is aimed at understanding intervention effectiveness, while the second-order randomization aims to understand the impact of specific cultural components by controlling for time participating in the intervention. Embedding the SCED in an RCT will allow for understanding how specific cultural components may provide immediate benefit and can inform future adaptation of the program if proven effective and scaled.

### Allocation, concealment, and implementation

The intervention allocation sequence will be generated using the “ralloc” command in Stata with 7 total strata (3 for age, 2 for gender, and 2 for site), a date-based randomization seed, and blocked randomization with blocks of varying size (8–16). Participants will be stratified by Head Start site, child gender, and child age to ensure equal groups of 3, 4, and 5 years old in each of the conditions. If more than one child in a family meets eligibility criteria, we will randomly select which child gets included in the study. We are unable to block randomize by parent gender because local feedback has suggested the majority are women.

Allocation will be handled by Research Electronic Data Capture (REDCap) electronic data capture tools hosted at Johns Hopkins University [49, 50]. The project data manager will generate the allocation tables describing the randomized order of allocation and upload them into REDCap’s randomization module, which will then implement all allocation. Once uploaded, REDCap will not allow the allocation tables to be accessed; thus, the allocation process will be concealed and protected from error. All evaluators will be blinded to participants’ study assignment and would only become unblinded if essential for management of the participant.

### Measures

Measures were selected for their strong psychometric properties and prior use and acceptance in Native American communities. Primary outcomes will be assessed at baseline (2 weeks), 6 weeks, 12 weeks, 6 months, 12 months, 12 months, 18 months, and 24 months. Table 3 outlines the detailed measurement schedule with corresponding time points for assessment. Assessment modalities include parents’ self-reports, and parents’ and teachers’ reports on children, allowing for rigorous analysis and triangulation of results. Measures are described by aim below.

**Table 3 Tab3:** Outcome measures and assessment time points

	# of items	Baseline	Pre-session 1	Each session	6 weeks	12 weeks	6 months	12 months	18 months	24 months
**AIM 1**										
***CAREGIVER: Mental/Emotional***										
PTSD Checklist for DSM-5	13	x			x	x	x	x	x	x
Parenting Stress Index - Short Form	20	x			x	x	x	x	x	x
Stressful Life Events Questionnaire	13	x								
CESD-R-10	10	x				x		x		x
Benevolent Childhood Experiences	10	x								
Adverse Childhood Experiences	17	x								
***CAREGIVER: Physical***										
Parenting Practices Interview	72	x				x		x		x
Parental Locus of Control	47	x				x		x		x
Family Routines Index	28	x				x		x		x
WHO ASSIST	10	x				x		x		x
***CAREGIVER: Spiritual***										
Historical Trauma	3	x								
Historical Loss Scale	12	x								
Communal Mastery Scale	10	x				x		x		x
Orthogonal Cultural Identification Scale	6	x				x		x		x
Historical Trauma Checklist	16	x								
***CHILD: Mental/Emotional***										
Strengths and Difficulties Questionnaire	30	x					x	x		x
***CHILD: Physical***										
School Attendance	–	x			x	x	x	x	x	x
**AIM 2**										
Perceived Stress Scale	10	x	x	x		x	x	x	x	x
**AIM 3: SOCIAL NETWORKS SUPPLEMENT**										
Caregiver Ego Networks	17	x				x		x		x
Columbia Suicide Severity Rating Scale	6	x				x		x		x

***Aim 1:***
*To evaluate the effectiveness of community health worker delivered Little Holy One on parent and child behavioral and mental health outcomes, using a randomized controlled trial design.*

Primary outcomes – Parent:Change in parent trauma symptoms will be self-reported at 2 weeks to 24 months using the *Post-Traumatic Stress Disorder (PTSD) Checklist for the Diagnostic and Statistical Manual of Mental Disorders (DSM) -5* (PTSD Checklist for DSM-5, Civilian Version) [51].Change in caregiver parenting stress will be self-reported using the *Parenting Stress Index – Short Form* (PSI-SF). The PSI-SF is a 36-item self-report that measures three domains of parenting stress: parental distress, parent-child dysfunctional interaction, and difficulty with child [52]. Scores range from 36 to 180. Score ranges are represented as percentiles; 15–80 is considered a typical stress percentile, 81–89 is considered a high stress percentile, and 90–100 is considered a clinically significant stress percentile. The PSI-SF was used in previous studies with Native American populations and performed well [27, 31, 34, 35].

Secondary outcomes – Parent:Change in parent depression symptoms will be measured by self-report with the *Center for Epidemiologic Studies Depression Scale-Revised* (CESD-R-10) [53]. The CESD-R-10 is comprised of 10 items based on DSM-IV diagnostic criteria for Major Depressive Disorder. Scores range of 0–30, with a score greater than eight indicate clinically significant symptoms. The CESD-R-10 is based on the CESD, a widely validated instrument, including among Native American populations [27, 34, 53, 54].Stressful Life Events will be assessed using the *Stressful Life Events Screening Questionnaire* (SLESQ)**,** a 13-item self-report questionnaire designed to assess lifetime exposure to potentially traumatic events [55, 56]. It has been used in several culturally diverse settings and is recommended for use for research purposes [55].Parents’ positive childhood experiences will be measured by self-report at baseline with the *Benevolent Childhood Experiences Scale* [57]. This is a 10-item scale designed to assess positive childhood experiences in adults with experience of mistreatment or adversity.Parents’ ACEs will be measured by self-report at baseline with a 23-item ACEs scale adapted to the study population [58].Parenting practices will be measured by the *Parenting Practices Interview* (PPI), a 72-item self-report questionnaire adapted from the Oregon Social Learning Center’s Discipline Questionnaire and revised for young children [59]. It measures the disciplinary style of a parent and has been used in a variety of settings and populations [60].Parental control will be measured by the *Parental Locus of Control Scale* (PLOC), a 47-item questionnaire which measures five factors to assess the locus of control a parent or caregiver has over a child [9].Family routines will be measured via self-report using the *Family Routines Index,* a 28-item questionnaire which measures 10 areas of family routines [61].Parent substance use will be measured via self-report using an adapted version of the 15-item *WHO ASSIST Questionnaire* [62], which screens for problematic or risky substance use. A risk score is provided for each of the 10 substances included in the survey. The ASSIST is reliable, valid, flexible, comprehensive, and cross-culturally relevant having been validated with populations all over the world [62, 63].Parent historical loss experiences will be assessed via self-report at baseline with the *Historical Loss Scale.* The scale quantifies 12 types of losses that Native American tribes might have experienced in the past, how often they are thought about in the present, and 12 different symptoms that they might have because of thinking about these losses [64]. This scale has been used in the previous study (α = .93) and in several Native American populations [65–67].Parent communal mastery will be measured via self-report using the 10-item *Communal Mastery Scale* [68, 69], which was developed specifically for Native contexts using two commonly employed measures of mastery and self-efficacy and adapted to add more collectivist statements. This scale was successfully used in a previous study at Fort Peck (α = .85).Parent tribal identity will be assessed using a modified version of the 6-item *Orthogonal Cultural Identification Scale.* The scale has been adapted for Assiniboine and Sioux tribal identity and was also used in a previous study on the Fort Peck Reservation (α = .90) [70, 71].Parents’ experiences related to historical trauma will be measured by the *Historical Trauma Checklist*. This measure is a 15-item checklist, developed from focus group discussions with the Fort Peck Reservation [24]. Three questions are posed to determine relevant historical trauma experiences.

Secondary outcomes – Child:The *Strengths and Difficulties Questionnaire* (SDQ) and impact supplement will measure childrens’ externalizing and internalizing behavior via parent report. The SDQ is a 30-item scale which measures 25 attributes on five scales: emotional symptoms, conduct problems, hyperactivity/inattention, peer relationship problems, and prosocial behavior [72].Head Start school attendance will be tracked via teacher report on an ongoing basis for all children enrolled in the study.

***Aim 2****: To explore the benefit of specific cultural enhancements (promoting tribal identity and communal mastery) of the intervention on caregivers’ mental health and well-being, by using a single-case experimental design embedded within the randomized controlled trial*.

Outcomes:Parent stress will be measured using the *Perceived Stress Scale* (PSS). The PSS is a 10-item scale that has been widely used and validated, including in Native American populations [73, 74].Parent communal mastery will be measured using the same 10-item *Communal Mastery Scale* highlighted above [68, 69].Parent tribal identity will be assessed using a modified version of the 6-item *Orthogonal Cultural Identification Scale* as highlighted above [70, 71].

***Aim 3****: Explore how the social network characteristics (*i.e.*, network size, average strength of ties, heterogeneity, density, % same race, % same age, % same gender) of American Indian parents/adult caregivers are related to both risk for and protection from suicide and opioid use*. ***Aim 3a****: Examine the impact of the Little Holy One family-based prevention program on the social networks of Native American parents/adult caregivers.****Aim 3b****: Determine whether program effects on social networks mediate effects on suicide and opioid among parents/caregivers*.

Outcomes:Social networks information will be collected via a 17-item self-report *Caregiver Ego Networks Questionnaire.* Parents will provide information about tribal affiliation, relationships, substance use, communication, parenting support, and cultural involvement of up to 10 of their closest social relationships [75, 76].Suicide risk will be measured with six items from the *Columbia Suicide Severity Rating Scale* (CSSR-S), which has been widely used to identify and assess individuals at risk for suicide across diverse communities and settings [77].

### Sample size and power

#### Aim 1

We based our primary sample size calculation on previous Family Spirit results indicating small to medium effect sizes for adult and child socio-emotional and behavioral outcomes 6 months post intervention completion [27, 31]. As such, power is based on detecting a small-medium difference between Little Holy One and control participants on caregiver and child outcomes 6-months post intervention completion (see below for power at 24 months post intervention). Since power analysis for mixed-effects regression models is complex, we use the approach described by Hox and Hedges [78, 79]. In this approach there are three steps: 1) estimate the power for a single-level regression model, ignoring clustering. This is considered the target sample size; 2) Compute the actual sample size for the proposed study that ignores the impact of clustering and accounts for attrition; and 3) Generate the effective sample size by penalizing the actual sample size with the design effect formula (i.e., n_eff_ = n / [1 + {n_clus_ – 1} ρ]). If the effective sample size is equal to or larger than the targeted sample size, then power is considered sufficient to detect the effect of interest. In our case, for step 1 power is .80 to detect a medium effect of f = .18 with 120 single-level, independent observations. For step 2, our actual sample size of 120 caregivers and children, with 5 measurement points, yields 600 (non-independent) observations. Accounting for attrition based on our previous work with family-based prevention interventions (i.e., the final *Family Spirit* trial had 18% attrition after 39 months’ intervention) [34], we used a conservative 30% attrition rate and adjusted our actual sample size to 420 non-independent observations. For step 3, using the design effect formula, accounting for 30% attrition and assuming a conservative nesting effect of ρ = 0.3 (to account for additional nesting within schools), our actual sample size of 420 non-independent observations provides the statistical power of 190 independent observations as our effective sample size. The effective sample size is more than the estimate for the targeted sample size indicating sufficient power to detect a small effect (f = .13). Sample size calculations for *all* aims can be found in Table 4**.**

**Table 4 Tab4:** Sample size calculations

	N	α	Power (1-β)	Effect size (f)

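### Aim 1 power is stated for the difference 6 months after completion, but the effective size of 190 belongs to a difference averaged over five assessments

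*Protocol article*

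**What the plan says.** All of this is in the protocol article.

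- **Contrast.** Under Sample size and power, Aim 1, power is for the "difference between Little Holy One and control participants on caregiver and child outcomes 6-months post intervention completion". The text points to a separate 24-month calculation, so the claim is tied to a time.
- **Step 1.** "for step 1 power is .80 to detect a medium effect of f = .18 with 120 single-level, independent observations".
- **Step 2.** "our actual sample size of 120 caregivers and children, with 5 measurement points, yields 600 (non-independent) observations". For dropout, "we used a conservative 30% attrition rate and adjusted our actual sample size to 420 non-independent observations".
- **Step 3.** The design effect is applied "assuming a conservative nesting effect of ρ = 0.3", which the text says also covers nesting within schools. The result: "420 non-independent observations provides the statistical power of 190 independent observations as our effective sample size".
- **Conclusion.** The paragraph and the Aim 1 rows of Table 4 claim 80% power at f = 0.13.
- **Analysis.** Statistical methods, Aim 1, plans a mixed-effects model on five repeated assessments. Growth terms are chosen after looking at plots, and the final model adds condition and condition-by-time terms.

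**The concern.** The stated question and the formula do not match. Dividing all observations by 1 + (m − 1)ρ gives the information on each person's mean over m occasions. It suits a treatment difference that is the same at every occasion and is estimated by averaging over them. A difference 6 months after completion is one point in time. Each retained person has one score there, and the other visits help only through baseline adjustment or an assumed trajectory.

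The five occasions also appear to include baseline, where randomisation makes the expected difference zero.

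This is separate from the F-test arithmetic. If only that were corrected, the paragraph would print f = 0.20 as the effect detectable 6 months after completion, and that figure would still belong to the pooled contrast. A null result at that time could then be read as coming from a trial with 80% power for a smaller effect than it could reliably detect.

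**Working it through.** **Inputs.** 120 dyads, 1:1; five measurement points; 30% attrition; ρ = 0.3; α = 0.05; power 0.80 (Sample size and power; Table 4). Sidedness is not stated; two-sided is assumed. Power is from the noncentral F for two equal groups: df 1 and N − 2, noncentrality f²N.

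**1. The plan's figure.** 120 × 5 = 600; 600 × 0.7 = 420; 420/(1 + 4 × 0.3) = 420/2.2 = 190.9. The printed 190 reproduces, with five scores per person. The people behind it number 420/5 = 84, or 42 per arm.

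**2. Which five occasions.** Table 3 gives the primary outcomes seven distinct occasions: baseline, 6 weeks, 12 weeks, and 6, 12, 18 and 24 months. The 24-month calculation adds two time points, and 5 + 2 = 7. On that count the five are baseline, 6 weeks, 12 weeks, 6 months and 12 months. This is inferred; the paragraph does not list them.

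**3. The separate F-test error.** At N = 190 the detectable f is 0.20, and power at f = 0.13 is 43%. An f of 0.13 needs about 466 independent observations. The fall from 80% to 43% at f = 0.13 therefore has nothing to do with the contrast.

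**4. The contrast mismatch, no trajectory assumed** (single visit, or time as categories). The baseline-adjusted equivalent is 84/(1 − r²), where r is the baseline-to-follow-up correlation.

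| Basis | Equivalent N | Detectable f (80%) | Power at f = 0.20 |
|---|---|---|---|
| Pooled, as in the plan | 190 | 0.20 | 78% |
| One visit, unadjusted | 84 | 0.31 | 44% |
| Adjusted, r = 0.3 | 84/0.91 = 92 | 0.29 | 48% |
| Adjusted, r = 0.5 (assumed) | 84/0.75 = 112 | 0.27 | 56% |
| Adjusted, r = 0.7 (assumed) | 84/0.51 = 165 | 0.22 | 72% |

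A generalised least squares calculation on all five visits, with categorical time, equal baseline means and a common correlation of 0.3, also gives 92.3 at 6 months. Under that structure the other visits add nothing beyond baseline adjustment.

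**5. Linear divergence assumed.** Visits at 0, 1.4, 2.8, 6 and 12 months; 42 per arm; ρ = 0.3. Random slopes, where used, have an assumed variance of 0.2. Six months after a 12-week course is about month 8.8.

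| Read-out | Baselines | N_eff, no random slopes | N_eff, random slopes |
|---|---|---|---|
| Month 8.8 | equal | 190 | 153 |
| Month 8.8 | free | 143 | 121 |
| Month 6 | equal | 409 | 329 |
| Month 6 | free | 183 | 165 |

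Power at f = 0.13 runs from about 30% (121) to 75% (409). None reaches 80%.

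**6. Average over four post-baseline visits.** 84 × 4/(1 + 3 × 0.3) = 336/1.9 = 177; detectable f = 0.21, unadjusted.

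**The case against.** The best defence is that the plan does not propose a single-visit comparison. It proposes a mixed model with growth terms, and a growth curve read at one time does borrow from every visit. This stands in part. With linear growth the effective size at month 8.8 can equal 190, and at month 6 it can exceed it. The plan leaves the growth shape open, so neither the categorical nor the linear case is its default.

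Three stronger readings are tempting, and the documents do not support them.

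- **That the mismatch alone cuts power from 80% to 22–24% at f = 0.13.** Most of that fall, from 80% to 43%, is the F-test error, present even at 190. The mismatch accounts for 43% to 22–24%, and only when no trajectory is assumed.
- **That f of about 0.30 is the correct replacement.** It takes ρ = 0.3 as the baseline-to-follow-up correlation, whereas the plan gives it as a nesting effect that also covers schools. The direction is not fixed either. With one common ρ, 84/(1 − ρ²) equals 420/(1 + 4ρ) when 5ρ² + 4ρ − 4 = 0, at ρ of about 0.58. At 0.7 the one-visit figure is 165 against 420/3.8 = 111 pooled.
- **That baseline is certainly one of the five.** The counts point that way, but Lesson frequency and duration lists five assessments after baseline (12 weeks; 6, 12, 18 and 24 months), so another reading is possible.

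The documents also leave open whether the 6-month visit is counted from baseline or from completion, which is why both read-out times are shown.

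**Conclusion.** The point holds in limited form. The paragraph names a difference 6 months after completion and supports it with an effective size for a difference averaged over five occasions. The claimed 80% power at f = 0.13 is not reached under any analysis examined.

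The part due to the mismatch depends on the time model. With no trajectory assumed, the detectable f moves from 0.20 to 0.31 unadjusted, or to 0.22–0.29 adjusted at correlations of 0.7 to 0.3. With linear growth, the effective size may fall below, match or exceed 190.

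These figures assume a two-sided test, 84 retained and, for the growth models, the visit times and slope variance given above. The matter is worth correcting because the primary power statement rests on it, but it does not call the design or the enrolment into question.

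**What to change.** Name the contrast, then restate the Aim 1 power paragraph and the Aim 1 rows of Table 4 to match it. There are two options.

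- **(a) Average difference over the post-baseline assessments.** Leave baseline out of the outcome count. With four visits the effective size is about 177 and the detectable f about 0.21, unadjusted. The analysis section would then need to name that average as the tested effect, since it now tests condition-by-time terms.
- **(b) Difference 6 months after completion.** Give the detectable f from 84 retained parents: about 0.29–0.31 at a correlation of 0.3 with no trajectory assumed. State the assumed baseline correlation and the time model. If a growth shape is relied on, fix it in advance and give the figure that follows from it.

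Under either option, list the occasions counted. The children's row needs its own count, because Table 3 schedules the Strengths and Difficulties Questionnaire only at baseline, 6, 12 and 24 months.

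The cost is some rewording and a less favourable stated figure. No participants or visits are added.

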**Aim 1**				
Parents	120	0.05	0.80	0.13
Children	120	0.05	0.80	0.13

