#### 24-month outcomes

While not our primary outcome, based on our conceptual framework, effects on proximal outcomes should correspond to effects on more distal outcomes measured at 2 years post-intervention. As there are no other longitudinal follow-up intervention studies in Native American settings, we assume a very conservative 50% retention rate of our original enrolled sample. This will result in approximately *n* = 42 participants in each arm at *24-months post intervention* completion. With power set to 80% and alpha set to 0.05, with *n* = 42 participants in each arm, and an additional 2 assessment time points, we will be able to detect an average effect size of f = 0.20 (medium effect) on continuous outcome measures between the groups.

#### Aim 2

Using the same approach as our Aim 1 power calculation, we will be powered to detect a medium effect (f = 0.20) in level of perceived stress (PSS) following delivery of the cultural components.

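### Aim 1 detectable effects are misstated: by the protocol's own method, 120 observations detect f of about .26 (not .18) and 190 effective observations about .20 (not .13)

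*Protocol article*

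**What the plan says.** The Aim 1 paragraph under Sample size and power sets its goal thus: "power is based on detecting a small-medium difference between Little Holy One and control participants on caregiver and child outcomes 6-months post intervention completion". It then follows three steps.

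- **Step 1** is to "estimate the power for a single-level regression model, ignoring clustering", which gives the target sample size. The result reported is that "for step 1 power is .80 to detect a medium effect of f = .18 with 120 single-level, independent observations".
- **Step 2** takes 120 participants with 5 measurements each (600 observations) and removes 30% for attrition, leaving 420.
- **Step 3** divides by a design effect with ρ = 0.3. The paragraph says that the result "provides the statistical power of 190 independent observations as our effective sample size". Because this exceeds the target, it concludes by "indicating sufficient power to detect a small effect (f = .13").

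Table 4 carries f = 0.13 at alpha 0.05 and power 0.80 into both Aim 1 rows, parents and children. Its 24-month rows give f = 0.20 for 84 people. The 24-month text says "With power set to 80% and alpha set to 0.05" and counts two further assessments. Neither the sidedness of the test nor any covariate adjustment is stated.

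In Table 3 the "Strengths and Difficulties Questionnaire" (SDQ) is marked at baseline, 6, 12 and 24 months only.

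**The concern.** A sample of 120 split between two arms is usually associated with a detectable standardised difference of about half a standard deviation, which is f of about .26. A claim of f = .18 is well below that. A claim of f = .13 from 190 effective observations goes further, and it is reached by changing the effect size after the target of 120 had been set for f = .18.

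Table 4 is the published justification of the trial's size. If its Aim 1 rows are too favourable, a null result could be read as evidence against small effects that the calculation, done as described, does not cover.

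**Working it through.** **Inputs**, all from Sample size and power and Table 4: two arms, 1:1; alpha 0.05; power 0.80; N = 120; 5 measurements; 30% attrition; ρ = 0.3. Assumption: two-sided test, with one-sided also shown.

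**1. Effective sample size (reproduces).**
120 × 5 = 600; 600 × 0.70 = 420; design effect = 1 + (5 − 1) × 0.3 = 2.2; 420/2.2 = 190.9. The stated 190 is right.

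**2. Power for a single-level two-arm contrast.**
Noncentral F with 1 and N − 2 degrees of freedom and noncentrality λ = N f². For two equal groups, f = d/2.

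| Statement | λ | Power, two-sided | Power, one-sided | f at 80% (two-sided) | N needed for the stated f |
|---|---|---|---|---|---|
| f = .18, N = 120 | 120 × .0324 = 3.89 | 49.8% | 62.4% | .258 | about 245 |
| f = .13, N = 190 | 190 × .0169 = 3.21 | 43.0% | 55.6% | .204 | about 467 |

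**3. Consistency of the two statements with each other.**
For fixed power, N scales with 1/f², apart from a small degrees-of-freedom effect. If 120 observations sufficed for .18, then .13 would need 120 × (.18/.13)² = 230, which is more than 190. No choice of alpha or sidedness common to both removes this conflict.

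**4. Other rows of Table 4 by the same method.**
- 24 months: 84 people with 5 + 2 = 7 measurements give 84 × 7 / (1 + 6 × 0.3) = 588/2.8 = 210, and 80% power at f = .194. The table prints 0.20.
- Moderators: 60 × 5 / 2.2 = 136.4, and 80% power at f = .242. The table prints 0.24.

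Both agree with a two-sided 0.05 test. So about 210 effective observations are credited with f = 0.20, while the smaller 190 of Aim 1 are credited with 0.13. (I take 84 as printed; the 50% retention in that paragraph would not give 42 per arm, which is 70% of 60. That is a separate matter.)

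**5. Other readings tried.**
- f taken as f²: power 99.6% and 99.9%.
- f taken as a correlation: 50% and 43%.
- f taken as d: 17% and 14%.
- 120 and 190 taken as per-arm sizes: 79% and 71.5%.
- A covariate R² of 0.5: 79% and 71%.
- More numerator degrees of freedom: power falls.

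None gives 80% for both statements.

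**6. SDQ.**
The article does not say which five measurements are counted. If they are baseline, 6 weeks, 12 weeks, 6 months and 12 months, the SDQ has three of them: 84 × 3 / (1 + 2 × 0.3) = 157.5, f = .225. With all four SDQ visits: 84 × 4 / (1 + 3 × 0.3) = 176.8, f = .212.

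**The case against.** The best defence is that the planned analysis is not the one used in the power paragraph. Statistical methods, Aim 1, describes a mixed-effects model that tests condition-by-time terms, and for such a contrast within-person correlation helps. As an illustration, take a pre-post arm-by-time interaction in 120 people with an assumed correlation of 0.5: λ = 120 × .0169 × 2/0.5 = 8.11, and power at f = .13 is 80.6%. This shows that f = .13 could be defended under another test. It does not rescue the text as written. The article bases step 1 on single-level independent observations, states no such correlation, and the same set-up gives about 97% at f = .18, so step 1 still fails.

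The defence does rule out several stronger readings that a reader might infer:

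- *The trial has about half the power it states.* The 43% and 50% belong to the simplified formula at the effect sizes named. They are not the power of the mixed model.
- *The step-3 rule fails because 190 is below 467.* The rule compares the effective size with the step-1 target, printed as 120. The fault is in that target and in the change of f.
- *The parent figure gets worse if ρ exceeds 0.3.* That is true of an averaged between-arm contrast. It reverses for condition-by-time.
- *The whole children row should be replaced by an SDQ figure.* School attendance is also a child outcome and is marked at baseline and every follow-up column of Table 3.

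**Conclusion.** The point holds as an arithmetic error in the stated calculation. Under the protocol's own method the Aim 1 detectable effects are f of about .26 at 120 independent observations (d about 0.52) and about .20 at 190 effective observations (d about 0.41), against the printed .18 and .13 (d of 0.36 and 0.26). The printed .13 is too small by about a third: .13/.204 = 0.64.

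Two-sided testing is an assumption, but one-sided testing does not change the conclusion, and the conflict between the two statements needs no assumption about sidedness. The effective sample size of 190 is correct. An f of about .20 can still be called small to medium, so the trial's stated goal is not overturned; what falls is the claim of adequate power for a small effect. For the SDQ, the five-measurement figure does not apply.

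**What to change.** N stays at 120.

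1. In step 1, give f of about .26 for 120 independent observations, or keep f = .18 and restate the target as about 245. In the latter case the step-3 comparison (190 against 245) no longer supports the conclusion and must be reworded.
2. In Table 4, change both Aim 1 rows from 0.13 to about 0.20, and delete the sentence claiming sufficient power for a small effect. The alternative is to name the test that yields .13 (for example the condition-by-time contrast), with its sidedness, its assumed correlation and any covariate R², and to show that it reproduces.
3. Add a note to the children row that the SDQ is scheduled at four visits only, with f of about .225 if three measurements are used.

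The cost is a correction to one paragraph and one table, and a less favourable stated detectable effect. Recruitment, conduct and analysis do not change.
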